### Intervention

#### Development of the HF education DVD and manual

A HF DVD and accompanying manual was developed by the principal investigator guided by adult learning theory [47] and studies that have investigated the individual learning needs of HF patients, especially in Asia [48–51]. Both the DVD and HF manual have been reviewed by a panel of HF experts in Australia and verified for content and cultural validity by a panel of HF experts in Thailand. The DVD and HF manual have been tested for readability and comprehensibility by three HF patients and carer dyads, who reported both resources to be helpful in gaining knowledge and self-care skills as well as assisting in coping with HF.

The DVD contains nine chapters that explain key aspects in learning to live with and adjust to HF. Chapter headings are: 1) What is HF?; 2) How does HF make you feel?; 3) When you feel sick what should you do?; 4) How you can make your heart feel better?; 5) Your medicine; 6) Your health record; 7) Your HF action plan; 8) Tips for your family and friends; and 9) Conclusion. The DVD was developed in an easy and simple mode for patients and carers to readily absorb the information, using pictures that reflect the Thai cultural context. At the end of each chapter, a reflective question is asked to encourage the patient and their carer to interact and discuss openly potential issues (e.g. which of the symptoms is the hardest for me to manage?).

The written manual is based on the DVD chapters and combines information for both patient and their carers. The manual contains more detail than the DVD, including written material, pictures and health record forms. The HF manual is divided into easily recognisable, colour-coded chapters that correspond to the nine DVD chapters. Both patient and carer will be asked to read each chapter within the manual and also help each other to complete the reflective questions or activities at the end of each section.

#### Intervention group

Treatment fidelity will be used to guide the implementation of the educational program which consists of five processes including: design, training, delivery, receipt, and enactment [52, 53]. The dyads in the intervention will receive their usual care plus a single individualised patient-carer education session. Education sessions will be conducted in the teaching room of the outpatient clinic. Dyads will receive the HF manual and a 45 to 60 minute education session focused on HF self-care. At the end of the session they will receive instructions about using the DVD and manual with their primary carer and/or family members. In addition, the intervention group will receive scripted telephone calls for 15 minutes per week in the first month, fortnightly in the second month, and once a month for the third to sixth month. The purpose of the telephone call is to reinforce, support and counsel each dyad about the HF information provided and assess any ongoing learning needs. The principal investigator will use the teach-back method [54] with each telephone call and give the dyad an opportunity to ask questions. The teach-back method is a technique used by educators to recall, deliver messages, encourage, and check for understanding, with participants asked to repeat the information that has been imparted to them [54]. This technique has been used to assess learning and promote self-care in patients with chronic conditions [54–56]. Specifically, in patients with HF, the teach-back method has been found to be an effective approach used in evaluating and educating patients’ self-care abilities [57, 58].

#### Control group

The control group will receive usual care provided by a clinician that includes: routine follow-up, physical and laboratory examinations, and general medical advice. The carer of the HF patient will receive any additional information if requested. In addition, the control group will receive weekly telephone calls for the first month, fortnightly for the second month, and once a month for the third to sixth month. To reduce the potential of patient contact acting as a confounding variable, the control group will also receive matched telephone calls, although the content of these calls will differ to that of the intervention group by being of a generic nature. Thus the telephone calls for the control group will not contain information based on the family support intervention; instead they will discuss in general terms how the patient and carer are feeling. If the patient’s condition has deteriorated significantly they will be advised to go and see their doctor. In consideration of the principle of fairness, at the end of the six month follow-up period participants in the control group will be offered a copy of the HF DVD and accompanying manual.

#### Data collection

Before randomisation all dyads will complete baseline questionnaires. Outcome measures will be collected at three and six months at the outpatient clinic or via telephone interview. Data will be collected by research assistants who are not aware of study group allocation. Questionnaires will take approximately 45 to 60 minutes to complete.

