### Participant eligibility

Participants for this study will be a dyad consisting of a patient and their partner or family member that is identified as providing informal care. All participants will need to have sufficient comprehension to read Thai without the need for a translator. The patients will be aged 20 years or over, although with the increasing prevalence of HF in the elderly, it is envisaged that the majority will be above 50 years of age. The inclusion criteria for HF patients are: 1) a primary diagnosis of HF NYHA (New York Heart Association) class I to III confirmed by the treating doctor and determined by a history of typical signs and symptoms and physical examination [45] and, where possible, objective evidence of cardiac dysfunction on echocardiogram; 2) at least one family member residing with them; 3) contactable by telephone at home; and 4) a DVD player at home. The inclusion criteria for carers are: 1) living in the same household as the HF patient or someone of the patient’s own choice; and 2) aged 20 years or over. Participants will be excluded if they reside in an urban area, have a documented history of dementia or severe psychiatric illness, are unable to continue to follow the protocol, and have severe symptoms indicative of acute heart failure [24, 46] or complications from cardiac or disease or other life threatening comorbidities.

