#### Primary outcome measures

The primary outcome will be HF knowledge as measured by the Dutch Heart Failure Knowledge Scale (DHFKS) in patients. The carers’ primary outcome will be perceived control about managing their family member’s HF as measured by the Control Attitudes Scale (CAS).

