### Summary of outcome measure

#### Knowledge

*The Dutch Heart Failure Knowledge Scale (DHFKS)*
[63] is a self-report questionnaire consisting of 15 multiple choice items related to: HF in general (4 items), HF treatment (6 items related to diet, fluid restrictions and activity), symptoms and symptom recognition (5 items). The scale has a minimum score of 0 (no correct answer) and a maximum score of 15 (all answers correct), higher scores indicate better knowledge. The tool developed in the Netherlands and tested on 902 HF patients, was found to be reliable (Cronbach’s α .62) and valid [58]. The scale has been shown to be sensitive in differentiating between patients who had and who had not received education and counselling (*p* < .01) and has been widely used in clinical settings to evaluate patients’ HF knowledge [22, 64, 65].

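### The patients' primary knowledge test may be taken by telephone while only intervention dyads hold the study materials, so look-up is possible in one arm only

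*Protocol article*

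**What the plan says.** Under Data collection, the protocol article gives one rule for all follow-up outcomes: "Outcome measures will be collected at three and six months at the outpatient clinic or via telephone interview". It does not rank the two modes. The same section says that the data collectors do not know the allocation.

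Under Primary outcome measures: "The primary outcome will be HF knowledge as measured by the Dutch Heart Failure Knowledge Scale (DHFKS) in patients". Under Knowledge, this scale "is a self-report questionnaire consisting of 15 multiple choice items", with a score from 0 to 15 that counts correct answers. Carers take it too, as a secondary outcome.

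The arms differ in what they hold. Under Intervention group: "Dyads will receive the HF manual and a 45 to 60 minute education session focused on HF self-care", and at the end of that session "they will receive instructions about using the DVD and manual with their primary carer and/or family members". Under Control group, "at the end of the six month follow-up period participants in the control group will be offered a copy of the HF DVD", together with the manual. Eligibility requires patients to be "contactable by telephone at home; and 4) a DVD player at home".

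Under Process evaluation, participants' manuals are to be looked at during the six-month assessment, to see whether the activities were completed.

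**The concern.** Symptom, quality-of-life and attitude scales have no answer key, so having a book at hand during an interview matters little for them. A test scored right or wrong is different, because its result depends on the conditions under which it is taken. Both follow-up tests, at three and six months, fall in the period when one arm has been given reference material and the other has not. If some intervention patients answer by telephone with the manual within reach, the between-arm difference in DHFKS mixes knowledge gained with access to the material during the test. The hypothesis is about knowledge, so the second component is not the effect the trial sets out to estimate. Blinded collectors do not help here: blinding stops the assessor from influencing the score, but does not stop a respondent from consulting a book.

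**Working it through.** **1. The chain, link by link**

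| Link | Source in the protocol article | Status |
|---|---|---|
| DHFKS may be collected by telephone, with no stated preference | Data collection | stated |
| DHFKS is the patients' primary outcome, scored by correct answers | Primary outcome measures; Knowledge | stated |
| Intervention dyads receive the manual and are instructed in using it and the DVD with family | Intervention group | stated |
| Controls are offered both only after six months | Control group | stated |
| A telephone interview finds the patient at home, near the material | Participant eligibility (home telephone) | inferred |
| The manual answers DHFKS items | Topic overlap only | inferred |

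On the last link, the scale covers heart failure in general (4 items), treatment (6) and symptoms with their recognition (5). The DVD and manual chapters cover what heart failure is, how it feels, what to do when unwell, and medicines, and the manual is the more detailed of the two. The topics coincide. The article does not say that the items do.

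**2. The plan's own sample size (context only)**

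Inputs: effect size 0.65, power 0.80, two-sided alpha 0.05 (stated for the previous study and assumed to carry over).

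n per group = 2 × (1.960 + 0.842)² / 0.65² = 2 × 7.85 / 0.4225 = 37.2, so 38; the exact t-test gives 39.

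The stated 40 agrees if it means completers: 100 dyads / 2 × 0.8 = 40. Whether 40 means completers or enrolled dyads is a separate question and does not affect this point.

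**3. What a look-up bias could do**

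The documents give no telephone share, no look-up gain and no DHFKS standard deviation. Everything in this step is therefore an illustration under assumptions.

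- Bias b = f × g, where f is the share of intervention patients who look up answers and g is the items each of them gains.
- SD assumed 2 / 0.65 = 3.08, which treats the two-point difference quoted from the previous study as equal to 0.65 SD. Range 2.0 to 3.5; the upper end is the SD implied by 50 per group, two points and power 0.80.
- n = 40 completers per arm, no true effect, normal approximation.
- λ = b / (SD × √(2/n)). With SD 3.08 the denominator is 3.08 × 0.2236 = 0.688.
- False-positive rate = Φ(λ − 1.96) + Φ(−λ − 1.96).

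| f | g | b (points) | b / SD | λ | False-positive rate, SD 3.08 | Over SD 3.5 to 2.0 |
|---|---|---|---|---|---|---|
| 10% | 1 | 0.1 | 0.03 | 0.15 | 5.2% | 5.2% to 5.6% |
| 25% | 2 | 0.5 | 0.16 | 0.73 | 11% | 10% to 20% |
| 50% | 2 | 1.0 | 0.33 | 1.45 | 31% | 25% to 61% |

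The first row is practically nil and the last would be serious. Nothing in the documents says which is nearer the truth.

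**The case against.** The strongest reply is that the rule is the same for both arms, and that what is missing is operational detail which a journal article leaves to the full protocol or the assessors' manual. Much of this stands. Interview instructions may exist elsewhere, and the mode rule itself is neutral. What remains is that the published rule leaves the mode open for an outcome that can be looked up, and can be followed to the letter while one arm alone has the material.

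Second, the call is a live interview, not a posted form, and nothing suggests that look-up would be common. This stands, and it is why no size is claimed. A reader might infer that the telephone test is in fact open-book for the intervention arm, or that the manual contains the DHFKS answers. The article supports neither: the materials were developed from adult learning theory and studies of learning needs, and only the topics are seen to overlap.

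Third, patient and carer can confer in either arm and in either mode. That is correct, so conferring is not in itself a source of arm-specific bias. It is only a reason to test the two separately.

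Fourth, inspecting the manual at six months suggests that intervention dyads may attend in person then. This may reduce telephone use at that visit. It also means the manual may be at hand in the clinic, and that seeing it could reveal the allocation to the collector. Moving the test to the clinic is therefore not sufficient on its own.

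Fifth, telephone collection plausibly protects retention in a rural population for which 20% attrition is allowed. This stands, and is a reason to keep telephone as a fallback.

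**Conclusion.** The point holds in a limited form. As published, the collection rule permits look-up on the patients' primary outcome in one arm only, and any bias from this runs towards the intervention. It rests on two inferences: that telephone interviews reach patients at home, and that material on the same topics would help with the items. The size is unknown. The illustrated range of 0.1 to 1.0 DHFKS points reflects assumed inputs only. A reader might want to state the bias as a fraction of the expected effect, but the documents do not support that: they give no telephone share or look-up gain, and the two-point difference is attributed to a previous study, while this trial plans on a standardised 0.65. The sample size and power are not in dispute. The change is worth making because it is cheap, the outcome is primary, and the bias could not be examined afterwards if mode were not recorded.

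**What to change.** - Make the clinic visit the default for the DHFKS at three and six months, with telephone as the fallback for missed visits.
- In both modes and both arms, read the same instruction: put all materials away and answer without help. Test patient and carer separately.
- At six months, inspect the manual only after the DHFKS is complete, and have this done by an existing team member other than the blinded assessor.
- Record the mode of each assessment and report it by arm.
- Keep all scores, whatever the mode, in the primary analysis. Present any clinic-only analysis as supportive, and note that it selects on attendance after randomisation, which may differ by arm and by state of health.

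Cost: a few sentences of protocol text, one field on the data form, and some effort to schedule tests with clinic visits. Keeping the telephone fallback avoids adding to attrition. The sample size is unchanged.

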#### Primary outcome measures

The primary outcome will be HF knowledge as measured by the Dutch Heart Failure Knowledge Scale (DHFKS) in patients. The carers’ primary outcome will be perceived control about managing their family member’s HF as measured by the Control Attitudes Scale (CAS).

#### Secondary outcome measure

Secondary outcomes for patients will be self-care as measured by the Self-Care of HF Index (SCHFI) and HRQoL as measured by the Minnesota Living with HF (MLHF) questionnaire. For carers, secondary outcomes will be HF knowledge as measured by the Dutch Heart Failure Knowledge Scale (DHFKS) and HRQoL as measured by the Short-Form 12-item (SF-12) health survey.

#### Participant descriptive data

Participant clinical and socio-demographic characteristics will also be collected, including: number of social supports; education level; occupational status; health literacy (measured using a single question “How confident are you filling out medical forms by yourself?” [59]); cognitive assessment (measured using the Montreal Cognitive Assessment [60]); comorbid illness burden (measured using Charlson Comorbidity Index [61]); vital signs; cardiac- related history including cardiovascular risk factors and length of time living with HF; New York Heart Association functional classification [62]; and HF current treatment.

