### Randomisation

The investigator will derive the random allocation from a computer-generated sequence of random numbers. Each dyad will be randomised at a 1:1 ratio in blocks of ten to either the control (usual care) or intervention (family-based education plus usual care) group. The random allocation will be sealed in an envelope and retained by technical staff at each hospital to give to the research assistants. Once participants have consented to the study and baseline data has been collected, the research assistant will open the sealed envelope indicating the group allocation. In this way, the research assistant collecting baseline data will be unaware of which group participants have been allocated to.

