#### Data analyses and sample size calculation

Data collected will be entered into the Statistical Package for the Social Sciences (SPSS Inc.). Descriptive statistics will be used to analyse demographic data. The sample size calculation is based on changes in HF knowledge. In a previous study investigating HF knowledge as the primary outcome [22]), a sample size of 50 per group and allowing for a 10% attrition rate, had adequate power (0.80) with a two-sided 95% significance to detect a difference of two-points on the DHFKS between the intervention and control conditions in mean post-test versus pre-test changes on the DHFKS and 93% power to detect clinically significant difference in MLHF scores of 6-points. For this study, assuming a medium effect size (0.65) in the between-group differences on the DHFKS and allowing for a 20% attrition rate, the minimal sample size of 40 per group will have sufficient power (0.80). An independent t-test will be used to test the overall differences of the DFHKS, SCHFI, CAS, MLHF and SF-12 within the groups and between the control group and the intervention group at baseline and over three and six months. Two-way repeated measures analysis of variance (ANOVA) will be used to test the difference between groups and change overtime in each group of the main outcomes (DFHKS, SCHFI, CAS, MLHF and SF-12). Treatment failure and withdrawal will be considered on an intention-to-treat basis, with the aim of providing a more realistic estimate of the difference between the two groups.

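### The three- and six-month t-tests of patients' heart failure knowledge leave recorded, plausibly prognostic covariates unused: a modest, conditional loss of precision, not bias or a power shortfall

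*Protocol article*

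**What the plan says.** Under Primary outcome measures: "The primary outcome will be HF knowledge as measured by the Dutch Heart Failure Knowledge Scale (DHFKS) in patients". The Knowledge section describes the scale as 15 multiple-choice items scored 0 to 15, which "was found to be reliable (Cronbach’s α .62) and valid".

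Under Participant descriptive data: "Participant clinical and socio-demographic characteristics will also be collected, including: number of social supports; education level; occupational status; health literacy". The same list includes the Montreal Cognitive Assessment. No time of measurement is given for any item on it.

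Under Data analyses and sample size calculation, "Descriptive statistics will be used to analyse demographic data". That section then names two methods for all the outcome scales: an independent t-test at baseline, three and six months, and a two-way repeated measures ANOVA by group and time. Neither is given a covariate. Under Randomisation, "Each dyad will be randomised at a 1:1 ratio in blocks of ten"; stratification by education or cognition is not mentioned.

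**The concern.** The patients' primary outcome is a knowledge test given after a programme of reading, viewing and telephone teach-back. Education and cognitive function are natural candidates to predict such a score whichever arm a patient is in. If they do, a follow-up t-test leaves their contribution in the error variance, and the confidence interval for the patients' primary effect is wider than the recorded data require. A chance difference in schooling between arms would also move the t-test estimate, and the plan offers no pre-specified adjusted analysis to set beside it. At stake is precision that could be had without new data or patients.

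**Working it through.** **Inputs from the article.** Effect size and attrition: "assuming a medium effect size (0.65) in the between-group differences on the DHFKS and allowing for a 20% attrition rate". Size and power: "the minimal sample size of 40 per group will have sufficient power (0.80". Two-sided 5% testing is stated for the precedent study ("had adequate power (0.80) with a two-sided 95% significance to detect a difference of two-points on the DHFKS") and is assumed to carry over. Recruitment gives a minimum of 100 dyads, that is 50 per arm at 1:1.

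**The plan's own figure.** Normal approximation: n per arm = 2(1.960 + 0.842)²/0.65² = 37.2, rounded up to 38. The exact noncentral t calculation gives 39. Both agree with the stated 40. Since 50 × (1 − 0.20) = 40, the 40 is the evaluable number per arm and fits the 100 dyads. At 40 per arm the noncentrality is 0.65 × √(40/2) = 2.907 on 78 degrees of freedom, and power is 0.819.

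**Adding covariates to the follow-up comparison.** If covariates explain a share R² of the within-arm variance, the standardised difference becomes 0.65/√(1 − R²), the standard error is multiplied by √(1 − R²), and the effective sample size by 1/(1 − R²). The article gives no R², so these values are assumptions:

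| Assumed R² | 0.65/√(1 − R²) | Power, 40 per arm | SE reduction | Effective n gain |
|---|---|---|---|---|
| 0 | 0.650 | 0.819 | 0 | 0 |
| 0.02 | 0.657 | 0.826 | 1% | 2% |
| 0.05 | 0.667 | 0.838 | 3% | 5% |
| 0.10 | 0.685 | 0.857 | 5% | 11% |
| 0.15 | 0.705 | 0.876 | 8% | 18% |

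Degrees of freedom hardly matter: with five removed (73 left), power at R² = 0.15 is 0.875.

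**Gain beyond baseline DHFKS.** Let ρ be the baseline to follow-up correlation. Take two covariates, each correlated r with both baseline and follow-up DHFKS, and 0.4 with each other. Their average then has squared correlation q² = r²/0.7 with the score, because (1 + 0.4)/2 = 0.7. The full model has R² = ρ² + q²(1 − ρ)²/(1 − q²), and the effective sample size ratio against baseline-only ANCOVA is (1 − ρ²)/(1 − R²). All correlations are assumed.

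- Low end, ρ = 0.6 and r = 0.2: q² = 0.0571, R² = 0.36 + 0.0571 × 0.16/0.9429 = 0.3697, ratio = 0.64/0.6303 = 1.015.
- High end, ρ = 0.4 and r = 0.4: q² = 0.2286, R² = 0.16 + 0.2286 × 0.36/0.7714 = 0.2667, ratio = 0.84/0.7333 = 1.145.

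**Baseline DHFKS alone.** ANCOVA multiplies the t-test variance by 1 − ρ²: 0.84 at ρ = 0.4, 0.75 at 0.5 and 0.64 at 0.6. Over these ranges baseline DHFKS contributes more than the two other covariates add to it.

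**The repeated measures ANOVA.** Baseline DHFKS enters as a time point, so stable traits largely cancel from the group-by-time contrast. Adding them as between-subject main effects leaves that contrast unchanged unless they predict change. The gain above therefore concerns only the between-arm comparisons at three and six months.

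**The case against.** The strongest objection is that this is a preference, not an error. A journal article may leave covariates to a fuller plan, and the sentence on descriptive statistics does not say that these variables have no other use. The first half stands: nothing is contradicted, and the unadjusted randomised comparison is unbiased, with an interval that already allows for chance imbalance. The second half stands only in part. The article is not silent on method: it names an independent t-test, which cannot hold a covariate, so the comment is on a stated choice.

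The size of the gain is also assumed. The article gives no correlation between education or cognition and the DHFKS. Eligibility requires reading Thai and excludes documented dementia, which may narrow the spread of both. This stands, and is why the gain is given as a conditional range.

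A reader might infer three stronger points, none of which the article supports.

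- *That only 32 patients per arm remain (40 less 20%), with power of 0.73.* With 50 enrolled per arm, 32 evaluable would need 36% attrition; the planned 20% leaves 40.
- *That alpha of .62 leaves about 62% of follow-up variance for covariates to explain.* Taking alpha as reliability, the remainder after baseline is 1 − 0.62² = 0.616. Of that, 1 − 0.62 = 0.38 is measurement error that no covariate can remove, leaving at most about 0.24. Alpha is also internal consistency from the Dutch sample, and the Thai translation is still to be made, so it is not a firm ceiling on the correlation.
- *That imbalance in schooling passes directly into every planned estimate.* It can move the follow-up t-tests, but stable traits largely cancel from the group-by-time contrast.

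**Conclusion.** The point holds as a minor improvement to a stated method. The follow-up t-tests of patients' DHFKS use neither education nor cognitive score, although both are recorded. At 40 evaluable per arm and d = 0.65, adjustment would take power from about 0.82 to about 0.84 to 0.88, given an assumed R² of 5% to 15%. Once baseline DHFKS is in the model, the further gain is perhaps 1.5% to 14.5% in effective sample size; near the low end it is negligible. These figures assume two-sided 5% testing, a 0.65 standardised on the follow-up score, and covariates measured before randomisation. The design reaches its stated 80% power without the change.

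**What to change.** For patient DHFKS at three and six months, replace the independent t-test with a pre-specified linear model (ANCOVA) containing arm, baseline DHFKS, education level with its coding fixed in advance, and Montreal Cognitive Assessment total. Baseline DHFKS should come first, as it is probably the strongest recorded covariate.

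Before adopting the model, confirm that education and the cognitive assessment are measured before randomisation. Data collection places the baseline questionnaires there, but Participant descriptive data gives no timing. Fill missing covariate values simply, for example with the overall mean or a missing category, chosen without reference to arm, so that no randomised patient is dropped on that account. Report the unadjusted t-test as a sensitivity analysis.

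The cost is a sentence or two of analysis text, a few degrees of freedom out of 78 (depending on the number of education categories), and the need to fix covariates and coding before unblinding. No further data or patients are needed. Pre-specification also removes the temptation to choose covariates after an imbalance has been seen.
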